Between 50% and 70% of men starting AS will receive either radical or palliative treatment over the following 10 years.^12^,^14^ In most men, radical treatment is initiated due to either a rising PSA or changes in Gleason grade on biopsy. Both are surrogate measures for disease progression. Many men are reluctant to undergo multiple biopsies and so most AS programmes are heavily reliant on PSA kinetics. For example, 25% of men in the Gothenberg screening trial^14^ and 43% of men in the Toronto trial who started AS received radical treatment due to a rising PSA alone.^4^ PSA values reflect benign enlargement and inflammation within the prostate^13^ as well as cancer growth. Therefore, many men with rising PSA values may not have disease progression and may not need radical treatment. For example, 65% of men within the PRIAS study^13^ and 72% in a large US series^15^ had favourable histology at radical prostatectomy after a period of AS. Within the ProtecT RCT, 50% of men randomised to monitoring received radical treatment with a <2% mortality rate at 10 years,^12^ highlighting the potential for overtreatment.

Various approaches have been tried to improve compliance with AS, including pharmacological interventions. The REDEEM study group randomised 302 men with low-risk PCa to 0.5 mg daily Dutasteride or placebo.^16^ At 3 years, the Dutasteride group had 10% fewer men with disease progression (defined as increasing cancer burden on biopsy or undergoing radical treatment). The ENACT study group randomised 227 men with low or intermediate-risk PCa to AS with or without 160 mg daily Enzalutamide.^17^ The addition of Enzalutamide reduced progression (pathological or therapeutic) by 46% at 12 months, although no difference was present at 2 years, there were side effects with this agent and its cost poses financial challenges to healthcare providers (especially if for long term AS regimens).

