### Blinding

This is an open label study. Both participants and clinicians will be aware of the study arm to which they are randomised. While test results, for example, MRI scans and PSA values can make it obvious that a participant is taking finasteride, the following will be blinded (not informed) to treatment allocation:

Lead Trial Radiologist responsible for reviewing MRI scans.Lead Trial Pathologist responsible for reviewing histopathology.Independent PCa Progression Review Panel, made up of three urologists.

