### Usual care: AS

Men randomised to usual care will receive AS (see figure 1). Patients will not receive a placebo, as PSA and MRI changes make masking impossible, blinding PSA data would be impractical since men may actively seek PSA tests outside the study, it is ethical that control participants experiencing any side effects, for example, erectile dysfunction, know they are independent of the treatment, participants unaware they are taking finasteride may opt for radical treatment earlier, and placebo controlled trials are expensive. Concerns regarding PSA changes or digital rectal examination changes will lead to MRI scans outside the schedule. Changes in MRI and PSA will lead to either a rebiopsy (to detail histological grade) or radical treatment. Radical treatment without radiological or pathological evidence of progression is discouraged but not prohibited.

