### Finasteride plus AS

Men randomised to the intervention group will receive finasteride (oral 5 mg) to be taken once a day for 2 years, in addition to AS (as above). Participants will be prescribed finasteride on a 3 monthly basis and this will be dispensed from their recruiting hospital pharmacy. Compliance will be measured using pill counts and patient questionnaires.

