Box 1Secondary objectives and outcomes within the Finesse trial.Outcome measuresTime until cessation of AS due to initiation of:ADT and/or chemotherapy.Radical prostatectomy.Radical radiotherapy.Timepoint(s) of evaluation of this outcome measure (if applicable):All occurrences of cessation of AS events due to (1) ADT initiation, chemotherapy, (2) radical prostatectomy (3) radical radiotherapy, (4) other treatment including watchful waiting and (5) death from prostate cancer during participant follow-up, 4 years on average, will be included in the analysis.The listed reasons for AS cessation will be treated as competing events. Cumulative incidence plots will be presented with a curve for overall AS cessation and for cessation for the individual post-AS treatment.To measure prostate cancer progression.Outcome measuresProgression is defined as either:Increase in MRI stage from T2a to ≥T2 c, T2b to ≥T2 c, or T2x to ≥T3 b.^27^Increase in grade from gleason 3+3 to ≥3+4 or 3+4 to ≥4+3.Radical Prostatectomy histology revealing grade ≥4+3 or stage ≥T3 a.PSA progression defined as ≥25% increase from the highest prerandomisation PSA value.Radiological confirmation of metastatic prostate cancer including identification via bone and/or PSMA PET scans.Clinical record of cancer progression.Clinical record of the initiation of palliative care.Death from prostate cancer.Clinical digital rectal examination (DRE) deterioration*.Extraprostatic disease.(note *DRE results alone will not be considered a definitive endpoint).Timepoint(s) of evaluation of this outcome measure (if applicable):To measure PCa mortality.Outcome measuresParticipant death from PCa.Timepoint(s) of evaluation of this outcome measure (if applicable):All deaths from PCa occurring during the 3–5-year follow-up of the study will be analysed.To study the changes in MRI appearances of the prostate over time in men with/without finasteride.Outcome measuresbpMRI/mpMRI scan results at baseline (the diagnostic MRI), 12 and 36 months (please note, a 36-month MRI scan is strongly recommended).Timepoint(s) of evaluation of this outcome measure (if applicable):Baseline, 12 and 36 months.Additional information:We will record:Prostate volume from (height, width, length).PCa stage: using the Prostate Imaging Reporting and Data System (V.2) and Tumour, Nodes, Metastasis staging.PCa size: taken as the maximum diameter on an axial slice from the MRI acquisitions.The pMRI/mpMRI images will be quality controlled centrally by the Lead radiologist. Full details can be found in the FINESSE Radiology Manual.To understand the views of patients and healthcare professionals regarding the use of finasteride within AS for this disease.Outcome measuresSemistructured one-to-one interviews led by a trained interviewer, with selected individuals during the follow-up phase.Timepoint(s) of evaluation of this outcome measure (if applicable):Months 48– 60To measure the rate of intervention for symptoms related to benign prostate enlargement:Defined as the use of oral medication (such as alpha blocker, PDE5 inhibitor or anti-cholinergic) or endoscopic prostate surgery (such as Transurethral resection of the prostate (TURP), Urolift, Green light laser TURP, steam treatment, Holmiun Laser Encucleation of the Prostate (HOLEP) or similar).Outcome measuresPatient self-reporting.Timepoint(s) of evaluation of this outcome measure (if applicable):All symptoms during the follow-up of between 3 and 5 years until trial end.Additional information:Determined from new prescriptions for oral medication (such as alpha blocker, PDE5 inhibitor or anti-cholinergic) or the participant undergoing a prostate surgery for benign enlargement (such as TURP, Urolift, Green light laser TURP, steam treatment, HOLEP or similar).Overall (all cause) mortality.Outcome measuresDeath electronic Case Report Forms (eCRF) completed by sites.Timepoint(s) of evaluation of this outcome measure (if applicable):All deaths during the follow-up of between 3 and 5 years until trial ends.Additional information:Cause of death will be decided by note review (and CRF completion) and death certificates.

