## Sample size

We estimate finasteride will reduce AS cessation rates by 50% (from 20% to 10%) after an average of 4 years follow-up. The sample size of 550 men (275 perm arm) is based on a time to event analysis with 90% power to reject H0: HR≠1, that is, the detection of a significant difference in AS cessation rates between arms by use of a two-sided log-rank test with alpha=0.05. We assume that 50% of control participants will progress (or be treated) during follow-up and that the HR is 0.65. The exact number needed is 271 per arm. We believe we will need to screen 1500 men to obtain 550 eligible, consenting recruits.

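### Box 1 counts a 25% PSA rise as progression with no confirmatory reading stated; chance crossings would fall mainly on control and tend to favour finasteride

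*Protocol article*

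**What the plan says.** Box 1 (Objectives and outcomes) defines progression by a list in which any single item suffices. One item is "PSA progression defined as ≥25% increase from the highest prerandomisation PSA value". The item gives a threshold, a reference and a direction. It mentions no repeat reading, and the threshold is the same in both arms. One other item carries a restriction: "DRE results alone will not be considered a definitive endpoint".

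The Introduction warns about this marker. It says that "PSA values reflect benign enlargement and inflammation within the prostate", as well as cancer growth, and that "many men with rising PSA values may not have disease progression and may not need radical treatment".

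On the drug, the plan gives "finasteride (oral 5 mg) to be taken once a day for 2 years". The section on usual care says "PSA and MRI changes make masking impossible", and the Blinding section says "MRI scans and PSA values can make it obvious that a participant is taking finasteride".

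The section on the PCa progression panel has independent urologists review every progression or cessation case. They may find progression present or absent, and they classify its type; biochemical is one of the types named. Table 1 defines the primary outcome by treatment, death from prostate cancer or leaving surveillance, not by Box 1.

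**The concern.** The trial exists partly because PSA rises are over-read as progression, yet its own progression outcome accepts such a rise without stating that it must be repeated. PSA is tested regularly for 3 to 5 years, so a man whose cancer is unchanged has many chances to cross the threshold once. The authors did consider which signs are too weak to stand alone, since they restricted rectal examination, but they did not restrict PSA.

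What is at stake is the third study aim, whether finasteride reduces disease progression. If chance crossings are common and fall unevenly on the arms, the comparison of overall progression is distorted, and the direction of the distortion matters.

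**Working it through.** **The plan's own figures.** The document gives no expected rate for the PSA component. Its sample size belongs to surveillance cessation and is unaffected. It reproduces: Freedman's formula at HR 0.65, two-sided 5% and 90% power gives 234 events, and 234 / (0.5 + 0.363) = 271 per arm, where 0.363 = 1 − 0.5^0.65.

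**Inputs from the document.** Threshold 1.25 times the highest pre-randomisation PSA; finasteride for 2 years; follow-up of 3 to 5 years, with the sample size reckoned "after an average of 4 years follow-up".

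**Assumptions not in the document.**
- Within-man variation is log-normal with CV 10, 15 or 20%, and there is no true change.
- The reference is the highest of k = 2 earlier readings (range 1 to 3).
- PSA is read at the Table 2 visit months (3-monthly to month 24, then 6-monthly), giving 12 readings by month 48. The actual schedule is in Figure 1, which is not shown.
- Finasteride lowers PSA to 0.5 of baseline (also tried: 0.7) from month 6 to month 24, with half the log effect at month 3 and full recovery by month 30. The document says PSA changes visibly on the drug but gives no size.

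**One reading.** With s = √ln(1 + CV²), CV 15% gives s = 0.149. Against a single baseline value, the chance that one follow-up reading crosses is P(Z ≥ ln 1.25 / (s√2)) = P(Z ≥ 0.223 / 0.211) = P(Z ≥ 1.06), about 14%. Repeated readings accumulate this; taking the highest of several baselines reduces it.

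**Repeated readings.** Simulation of 100,000 stable men per cell, k = 2, percentage crossing at least once:

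| | CV 10% | CV 15% | CV 20% |
|---|---|---|---|
| Control, to month 24 | 9 | 27 | 40 |
| Finasteride (0.5), to month 24 | 0.0 | 0.02 | 0.4 |
| Finasteride (0.7), to month 24 | 0.02 | 0.7 | 4 |
| Control, to month 48 | 12 | 33 | 48 |
| Finasteride (0.5), to month 48 | 5 | 17 | 27 |
| Two consecutive readings, control, month 48 | 1.1 | 6.7 | 13.5 |
| Two consecutive readings, finasteride (0.5), month 48 | 0.4 | 2.5 | 5.5 |

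Over k = 1 to 3 and CV 10 to 20%, the single-reading range at month 48 is 6% to 67% in control and 2% to 47% on finasteride.

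**Why the arms differ.** A man whose PSA is at 0.5 of baseline must rise by 1.25/0.5 − 1 = 150% from his treated level to reach the threshold; at 0.7 it is 79%. A control man needs 25%. Nearly all finasteride crossings come after the drug stops.

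**Effect on the comparison.** Take true progression as 30% in both arms (assumed), so there is no drug effect. The cumulative hazards are h = −ln 0.70 = 0.357 for true progression, and −ln 0.67 = 0.400 (control) and −ln 0.83 = 0.186 (finasteride) for chance crossings. The apparent ratio at month 48 is (0.357 + 0.186) / (0.357 + 0.400) = 0.72. With true progression of 20% or 50% it is 0.66 or 0.80. With confirmation, the 30% case gives (0.357 + 0.025) / (0.357 + 0.073) = 0.89. These are ratios of cumulative hazards before panel review.

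**Benign upward drift.** If PSA also rises 3% a year (1.03⁴ = 1.126 over four years, below the threshold by itself), then at CV 15% and k = 2 single crossings are 49% in control and 36% on finasteride. Two consecutive readings give 14% and 9%.

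**The case against.** The strongest objection is that the article is condensed. A repeat-test rule could sit in the full protocol, and the published text is silent rather than explicit that one value suffices. That stands and limits confidence. Against it, the published item is otherwise complete, and the list found room for a caveat on rectal examination.

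Second, two features soften the problem. Using the highest pre-randomisation value lowers chance crossings: at CV 15%, the control figure at month 48 falls from 54% with one baseline to 22% with three. The panel reviews each case and can find no progression, so the percentages above are crossings before adjudication. A reader might infer that nothing stands between a noisy value and the outcome; the panel section does not support that. The protection is partial, though. No stated criterion tells the panel to set aside a rise that meets Box 1, biochemical progression is a class it may assign, and the PSA values it would need to see can reveal the arm.

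Third, a reader might infer that the noise is the same in both arms and only dilutes a real effect. That does not fit a reference fixed before treatment together with a drug that the document says visibly changes PSA.

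Fourth, confirmation does not cure everything. Benign enlargement persists, so a second reading would often confirm it, and an imbalance between arms remains. This is correct and is why the fix has two parts.

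**Conclusion.** The point holds for the rule as published. At CV 15% with two baselines, about a third of stable control men would meet the PSA item by month 48. With on-drug PSA at half of baseline, the finasteride figure is about 17%. The tendency is to favour finasteride: with no true effect, the apparent ratio would be about 0.72 under the stated assumptions. The sizes depend heavily on the CV, the number of baseline readings, the test schedule and the drug's effect on PSA, none of which the document gives. The direction requires only that finasteride lowers PSA against an untreated reference.

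A reader might go further and infer that the third aim cannot be answered, or that the primary result is affected. Neither follows. The abstract lists rates and type of progression, and the panel classifies each event, so pathological and radiological progression can be read separately. The primary outcome does not use this definition. The rule should be changed, but the fault is confined to a secondary outcome.

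**What to change.** In the Box 1 outcome definition, count PSA progression only when the rise of 25% or more is confirmed on the next available PSA, dated at the first of the two readings. Record unconfirmed rises without counting them as events. If the full protocol already contains such a rule, state it in Box 1. At CV 15% this takes chance labels from about 33% and 17% (control and finasteride) to about 7% and 2.5%.

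Because control still carries about 2.7 times as many (6.7 / 2.5), also report progression without the PSA component as a sensitivity analysis, using the panel's classification.

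The cost is a change of wording and one extra analysis on PSA values already collected. It concerns what is counted as an event, not how men are tested or treated. The downsides are that a rise at the last visit stays unconfirmed and that some events are established one visit later.

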**Trial registration number:**

ISRCTN16867955

Strengths and limitations of this studyWhile active surveillance (AS) is an established method of managing men with prostate cancer, few studies have attempted to improve compliance with this regimen.Finasteride is widely available, has a known safety profile, is well tolerated and is used in a similar patient population for benign prostate enlargement.This study will determine AS outcomes in a contemporary cohort of intermediate-risk cancers.There remains some scepticism about the role of pharmacological prostate-specific antigen manipulation for AS patients.Pre-biopsy MRI may reduce the pool of eligible men and hamper recruitment.

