## Study aims

To understand whether the addition of finasteride to AS increases adherence in men with low/intermediate-risk PCa.To understand the tolerability and compliance with finasteride within an AS regimen.To understand whether the addition of finasteride to AS reduces disease progression in these men.

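### Judging PSA rise in both arms against untreated PSA tilts the secondary progression comparison towards finasteride

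*Protocol article*

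**What the plan says.** Box 1 of the protocol article (under Objectives and outcomes) defines cancer progression by a list of ten items, any one of which suffices. One is "PSA progression defined as ≥25% increase from the highest prerandomisation PSA value". The rule does not differ by arm, and the article gives no on-drug reference value, no correction, and no rule for the period after finasteride stops. Only one item is barred from standing alone: "DRE results alone will not be considered a definitive endpoint". PSA carries no such restriction.

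The article also says that the drug moves this measurement. Under Blinding, "MRI scans and PSA values can make it obvious that a participant is taking finasteride". Under Usual care, the absence of a placebo is justified "as PSA and MRI changes make masking impossible". The list of strengths and limitations adds: "There remains some scepticism about the role of pharmacological prostate-specific antigen manipulation for AS patients". The direction of the shift is implied by the trial's rationale, but neither direction nor size is stated.

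The third study aim rests on this outcome: "To understand whether the addition of finasteride to AS reduces disease progression in these men". Finasteride is given for 2 years in one arm only, and active follow-up lasts 3 to 5 years.

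**The concern.** The reference value is an untreated PSA for every man, but the later values are taken on drug in one arm and off drug in the other. A control meets the criterion when his PSA has risen by a quarter. A man on finasteride must first make up the pharmacological drop and then rise a quarter above his highest untreated value. The two arms face different hurdles even if their cancers behave identically.

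At stake is the reading of the third aim. A lower progression rate with finasteride could reflect a slower cancer, a suppressed marker, or both. The Introduction itself notes that PSA also reflects benign enlargement and inflammation, and that many men with rising values may not have progressed.

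**Working it through.** **1. The plan's own figure.** Inputs from Sample size: two-sided alpha 0.05, power 90%, 50% of controls with an event, HR 0.65. The article gives no figure for the PSA criterion, so the sample size is the only one to reproduce.

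- Events (Freedman) = (1.960 + 1.282)² × ((1 + 0.65)/(1 − 0.65))² = 10.51 × 22.22 = 233.5.
- Treated event proportion = 1 − 0.5^0.65 = 0.3627; mean of the arms = (0.5 + 0.3627)/2 = 0.4314.
- Total = 233.5/0.4314 = 541.3, or 270.7 per arm, which rounds to the stated 271.

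The calculation reproduces and uses no PSA quantity.

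**2. The hurdle on drug.** If finasteride lowers PSA by a fraction r and leaves the cancer alone, the underlying rise needed to reach 1.25 times the untreated reference is 1.25/(1 − r) − 1. The values of r are assumptions.

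| Assumed drop r | Underlying rise needed |
|---|---|
| 0% (control) | 25% |
| 20% | 56% |
| 30% | 79% |
| 50% | 150% |
| 60% | 213% |

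Any drop at all raises the hurdle in the finasteride arm only.

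**3. The two drug years.** Simulation with no effect on the cancer, 200,000 men per scenario. Assumed: lognormal within-man variation with CV 10% to 20%, reference equal to the highest of one or two baseline values, tests at 6, 12, 18 and 24 months, and an event at the first value over the threshold. With flat underlying PSA, 5% to 47% of controls meet the rule by month 24. On drug the figure is at most about 6% for a 30% drop and 0.2% for a 50% drop.

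**4. After the drug stops.** Same model at CV 15% with two baseline values, 6-monthly tests continued to month 48, and a 50% drop. Cells show control against finasteride.

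| Scenario | Month 24 | Month 48, full rebound | Month 48, suppression persists |
|---|---|---|---|
| No growth | 17% v 0% | 27% v 17% | 27% v 0% |
| 10% growth per year in both arms | 44% v 0% | 87% v 85% | 87% v 0.1% |

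A second model let growth differ between men (mean 3% to 10% per year, within-man SD of log PSA 0.10 to 0.15, highest of two baseline values). It gives the same picture. By month 24, 26% to 56% of controls meet the rule, against under 1% at a 50% drop. At month 48 with full rebound the figures are 43.2% to 70.8% against 39.5% to 64.9%. If suppression persists, the finasteride figure at month 48 is 0.7% to 13%.

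**5. Is re-baselining a safe repair?** Take every man's month-6 value as the new reference, require a confirmatory value, and assume flat underlying PSA with full rebound after month 24. By month 48 about 72% to 87% of finasteride men meet the rule at a 30% drop and 98% to 100% at a 50% drop, against 5% to 25% of controls. The bias reverses and becomes larger.

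**The case against.** Four points can fairly be made for the plan.

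- **Much of the effect is delay.** Finasteride stops at 2 years and follow-up runs to between 3 and 5. If PSA returns fully, the month-48 proportions come close together (87% v 85% in one scenario). This stands, and month-24 figures alone would overstate the problem. But delayed events still favour finasteride in a time-to-event comparison, and nothing in the article establishes a full rebound.
- **Progression is to be reported by type and reviewed by a panel.** The Abstract names rates and type of progression, and the PCa progression panel section has independent urologists agree whether progression is present and classify it, biochemical included. A reader might infer from Box 1 that suppressed PSA can never be separated from slower cancer; these provisions make that too strong. They do not remove the bias from the overall comparison. The panel reviews cases of progression or cessation, so it cannot recover finasteride men who never reach the threshold. It is also not told allocation, and the article gives it no rule for on-drug PSA.
- **PSA is one item of ten in a secondary outcome.** This stands. How far the composite is distorted depends on how many events are PSA-only, which the article does not say.
- **The full protocol, SAP or panel charter may hold an on-drug rule.** Possibly, but the article states the definition outright and without one.

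The item "Radical Prostatectomy histology revealing grade ≥4+3 or stage ≥T3 a" invites a stronger reading: that fewer operations would lower progression by a calculable amount. Such histology does exist only in operated men. A figure, however, would need adverse-histology rates borrowed from other cohorts, an assumed share of prostatectomies, and the premise that none of these men already counts through MRI or biopsy grade. The article supports a stated limitation, not an estimate.

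**Conclusion.** The point holds for the secondary progression outcome. As written, the PSA criterion biases the between-arm answer to the third aim towards finasteride with no effect on the cancer. For an assumed 30% to 60% drop, the underlying rise needed on drug is 79% to 213%, against 25% in controls. Events are nearly absent on drug at a 50% drop and at least delayed afterwards. The later gap runs from small (full rebound with steady growth) to very large (persistent suppression).

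This rests on the PSA shift being downward, which the article implies but does not state, and on assumed growth, within-man variation and test schedule.

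A reader might go further and conclude that the trial is bound to show less progression, or that its main result is compromised. Neither follows. The share of PSA-only events is unknown, and the primary outcome in Table 1 is built from treatment, death from prostate cancer and discontinuation of surveillance, not from a PSA threshold. The definition should be fixed, but it does not put the primary outcome definition or the sample size in doubt.

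**What to change.** For the between-arm progression comparison, do not let PSA rise alone count as progression, as is already the case for DRE. Report PSA rise separately and descriptively by arm. Show the composite with and without PSA-only events as a sensitivity analysis.

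Do not re-baseline all men at a single post-randomisation visit: the rebound when finasteride stops would then itself count as progression (step 5 of the working).

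State as limitations that prostatectomy histology is available only in operated men and that, under Usual care, off-schedule MRI and repeat biopsy are partly triggered by PSA. The article also says that MRI changes on the drug, so the remaining components are not wholly free of the problem. Report them by type.

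The change is to outcome wording and derivation, from data already being collected, and can be made while recruitment continues. The price is fewer counted events and a less precise progression comparison.

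### The drug part of the benign-enlargement outcome is identified by drug class without a stated indication, so prescriptions for erectile dysfunction or after radical treatment could be counted

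*Protocol article*

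**What the plan says.** All of this is in Box 1 of the protocol article (Objectives and outcomes), unless another section is named.

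- **Objective.** It limits the outcome to interventions for symptoms of benign prostate enlargement.
- **Definition.** "Defined as the use of oral medication (such as alpha blocker, PDE5 inhibitor or anti-cholinergic) or endoscopic prostate surgery", followed by examples of procedures.
- **Determination line (additional information), drugs.** "Determined from new prescriptions for oral medication (such as alpha blocker, PDE5 inhibitor or anti-cholinergic".
- **Determination line, surgery.** "the participant undergoing a prostate surgery for benign enlargement".
- **Source.** Patient self-report.
- **Window.** "All symptoms during the follow-up of between 3 and 5 years until trial end". No stop or censoring at radical treatment is given for this outcome.

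Two other places bear on it. The section Usual care: AS, explaining why there is no placebo, gives erectile dysfunction as its example of a side effect: "it is ethical that control participants experiencing any side effects, for example, erectile dysfunction, know they are independent of the treatment". The section Sample size expects the arms to differ in how many men leave surveillance: "We estimate finasteride will reduce AS cessation rates by 50% (from 20% to 10%) after an average of 4 years follow-up".

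**The concern.** The objective is defined by the reason for treatment, but the line that says how drug events are found is defined by drug class. The two coincide only if every new prescription in those classes is for benign enlargement. As general clinical knowledge (the article does not say so), PDE5 inhibitors are also prescribed for erectile dysfunction, and both PDE5 inhibitors and anticholinergics may be prescribed after prostatectomy or radiotherapy.

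Both routes could be unequal between arms. Erectile dysfunction is an effect that the article itself associates with treatment, so prescriptions for it could add events on finasteride. Radical treatment is expected more often in controls, so prescriptions after it could add events there. The comparison of benign-enlargement treatment would then mix the intended effect with two unintended ones of opposite sign. The trial is open label, and the independent panel reviews only progression and cessation of surveillance, so the article describes no check on how these self-reports are classified.

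**Working it through.** **1. The two halves of the determination line side by side**

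| | Drugs | Surgery |
|---|---|---|
| Identified by | new prescription in a named class | prostate procedure |
| Indication restated | no | yes, benign enlargement |
| Source | self-report | self-report |
| Stop at radical treatment | not stated | not stated |

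The definition line restates no indication for either half and relies on the objective above it. The determination line repairs this for surgery only.

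**2. The plan's own figures.** The article gives no expected rate, effect or power for this outcome, so there is no stated figure to correct. Its one computed figure is the sample size, which supplies inputs below. From "We assume that 50% of control participants will progress (or be treated) during follow-up and that the HR is 0.65", the finasteride event proportion is 1 − (1 − 0.5)^0.65 = 0.363. Freedman's formula with HR 0.65, 90% power and two-sided alpha 0.05 gives 234 events, and 234 / (0.5 + 0.363) = 271 per arm, as stated. This calculation does not depend on the benign-enlargement outcome.

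**3. Prescriptions after radical treatment.** Assumptions: all cessation is radical treatment, and a share s of those men (10% to 50%) start a listed drug for another reason. Extra events per arm = 275 × cessation proportion × s.

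- At 20% v 10%: controls 275 × 0.20 × s = 5.5 to 27.5; finasteride 275 × 0.10 × s = 2.75 to 13.75. Excess in controls = s × 10 points = 1.0 to 5.0 points.
- At 50% v 36.3%: controls 13.75 to 68.75; finasteride 10.0 to 49.9. Excess in controls = s × 13.7 points = 1.4 to 6.9 points.

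Both pairs are used because Sample size gives both. The second includes progression without treatment and so overstates radical treatment.

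**4. Prescriptions for erectile dysfunction.** Assumption: an excess e of 2% to 10% on finasteride. Extra events = 275 × e = 5.5 to 27.5 in that arm.

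**5. Net direction.** Ignoring overlap, the net spurious excess in controls is s × (cessation difference) − e.

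- At 20% v 10%: from 1.0 − 10 = −9.0 points to 5.0 − 2 = +3.0 points.
- At 50% v 36.3%: from 1.4 − 10 = −8.6 points to 6.9 − 2 = +4.9 points.

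The sign depends on inputs that the article does not give.

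**6. What this could do to a rate ratio.** Assume a genuine rate g and an independent unintended rate x, so that the observed rate is 1 − (1 − g)(1 − x).

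- Erectile-dysfunction route alone, genuine rates 10% (finasteride) v 15% (control), ratio 0.67. With x = 3%, 5% or 8% on finasteride, its observed rate is 1 − 0.90 × 0.97 = 12.7%, 1 − 0.90 × 0.95 = 14.5%, or 1 − 0.90 × 0.92 = 17.2%. The ratio becomes 0.85, 0.97 or 1.15.
- Radical-treatment route alone, no genuine difference (10% v 10%), cessation 10% v 20%, s = 50%. Finasteride 1 − 0.90 × 0.95 = 14.5%; control 1 − 0.90 × 0.90 = 19.0%; ratio 0.76.

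The genuine rates, s, e and x are illustrative, not trial figures.

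**The case against.** The best reply is that the objective already governs the list beneath it: the named classes are examples of interventions for benign-enlargement symptoms, so a drug for erectile dysfunction is excluded on a natural reading. The Abstract also describes the outcome as treatments received for benign enlargement. The article is condensed, and the medication question may already ask for the reason. This stands to the extent that a reader should not infer that prescriptions are counted whatever their reason. No text says so. What remains is that the determination line restates the limit for surgery and not for drugs, so literal application could depart from the objective.

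A reader might also infer that an adverse effect of finasteride is concealed inside this outcome. The documents do not support that. Tolerability is a separate aim with its own analysis, the data monitoring committee reviews safety data, and EPIC is collected to month 60, continuing after radical treatment with consent. Counting a prescription here removes it from none of these.

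Nor is the difference between use in the definition and new prescriptions in the determination line a firm contradiction: the second can fairly be read as making the first operational. Aligning them is still worthwhile, because men previously treated for benign enlargement are eligible.

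Finally, cessation includes systemic therapy, watchful waiting, cancer death and other reasons, so applying post-radical prescribing to all of it overstates that route. This stands, and it is why the figures are illustrations.

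**Conclusion.** The point stands as a gap in the operational rule of one secondary outcome. Drug events are identified by self-reported new prescription in named classes without the indication that surgery carries, and no handling after radical treatment is stated. Unintended prescriptions could therefore be counted, possibly unequally by arm. Under the assumptions shown, each route could add from about 1 to 10 percentage points to one arm relative to the other, in opposite directions, and the net sign is unknown. It does not follow that the between-arm result is biased in a known direction or is uninterpretable.

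The conclusion assumes that the listed drugs are prescribed for other reasons often enough to matter, that reporting of new medication continues after radical treatment (the article confirms this only for the quality-of-life questionnaires, with consent), and that the forms do not already record the reason. Severity is minor to moderate. The primary analysis, sample size and safety recording are unaffected.

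**What to change.** 1. Count a drug only when its recorded reason is lower urinary tract symptoms or benign enlargement, matching the surgery rule. Add one indication field to the existing medication question if it is not already there.
2. Use new prescription since randomisation in both the definition and the determination line.
3. Treat radical or systemic prostate cancer treatment as a competing event for this outcome, or at least report events before and after it separately.

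The cost is one form field, matching wording in the protocol and analysis plan, and a sensitivity analysis for prescriptions whose reason is unclear. Trial status reports that recruitment is still active, so the change is best made now: reasons for prescriptions are harder to recover later from self-report.
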